**Study C:**

From the questionnaires that will be used "24h recall' has the largest number of variables at 216 variables. Although, the number of necessary examples depend on the data itself, considering algorithms such as support vector machines will be used for the classification, we need at least the same number of examples as variables. This is because we will try to solve a system of linear equations, and to avoid and ill-conditioned system we need to have 1:1 relationship between variables and samples (Smola and Schölkopf, 2004). In addition, as we will divide our analysis into training and testing, we need an extra 10% of samples for testing and considering a measurement error of 5% puts the total of samples at 246.1 ~= 247 (upper limit). Thus, we need at least 247 samples for the analysis of the dataset.

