Taking together, although there are strong suggestions for the influence of maternal diet on breast milk composition, the scarcity of high quality studies and diversity in study design restrain the ability to draw strong conclusions. In addition, there is a lack of studies linking the maternal diet and associated breast milk composition to the gut health of the infant resulting in protection against respiratory infections and/or the development of allergies. There is a vast need for an observational study with a bigger sample size, which is also based on a power calculation (Bravi et al., 2016). Therefore, we plan to perform a substudy within the PRIMA human milk cohort. In this cohort (n=250), we will additionally assess the maternal diet, and collect feces and saliva of the infant. This study design allows to not only link the short- and long-term influence of maternal diet to breast milk composition, but also the clinical health outcomes in infants, with Medically Attended Respiratory tract Infections during the first year of life as main study parameter. Even more, the influence of the maternal diet

and an infant’s antibody repertoire on intestinal microbial composition, and subsequently on the risk of developing RTIs is explored.

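### Study C's sample size rests on a 1:1 samples-to-variables rule that does not prevent ill-conditioning and is not needed for the method named, and its test allowance of about 22 infants is too small to judge a classifier

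*Protocol*

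**What the plan says.** Protocol section 4.4 (Sample size calculation, Study C) starts from the questionnaire with the most items, the 24h recall, which "has the largest number of variables at 216 variables". It expects to classify with algorithms such as support vector machines and concludes that "we need at least the same number of examples as variables". The reason given is that "to avoid and ill-conditioned system we need to have 1:1 relationship between variables and samples". It then makes two allowances: "an extra 10% of samples for testing and considering a measurement error of 5% puts the total of samples at 246.1". This total is rounded up to give a minimum of 247.

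The Study C part of section 1 plans a slightly larger group: "In this cohort (n=250), we will additionally assess the maternal diet". It names medically attended respiratory tract infection (MARI) in the first year as the main study parameter, and it argues that the field needs a larger study sized by a power calculation. Section 4.4 gives no alpha, power, effect size, outcome rate or target precision for Study C, and does not name the outcome to be classified.

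**The concern.** The rule is the only support for Study C's size. If it does not do what it is said to do, then 247 says nothing about how well a diet-based classifier will perform or how precisely that performance will be known.

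Three things look wrong. A 1:1 ratio is offered as protection against ill-conditioning, although it is where that problem peaks. The total does not follow from the stated inputs. The samples set aside for testing are few. At stake is how the results linking maternal diet to infant infection risk (secondary objectives 7 and 9 in section 2) can be read. With a very small test set, the reported performance would be largely noise.

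**Working it through.** **Inputs.** From section 4.4, Study C: 216 variables, +10% for testing, +5% for measurement error, stated total 246.1 rounded up to 247. From section 1, Study C: n = 250. Assumed here because the protocol gives no value: a true AUC of 0.70, and MARI rates of 10%, 20%, 30% and 50%.

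**1. The stated total**

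- Allowances added: 216 × 1.15 = 248.4, so 249.
- Allowances compounded: 216 × 1.10 × 1.05 = 249.48, so 250.
- The printed decimal: 214 × 1.15 = 246.1 exactly.

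Neither plain reading of 216 gives 246.1. The exact match suggests that 214 variables were used in the calculation. The difference is 2 to 3 samples, and n = 250 covers both results.

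**2. The conditioning argument**

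The condition number (largest over smallest non-zero singular value) was simulated for n × 216 matrices with independent standard normal columns, 60 matrices per n. Medians:

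| n | Median condition number |
|---|---|
| 108 | 5.5 |
| 216 | 803 |
| 222 | 107.5 |
| 247 | 26.7 |
| 324 | 9.5 |
| 432 | 5.6 |
| 2160 | 1.9 |

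The peak is at n = 216, the ratio the protocol sets as its safeguard. Correlated dietary items would generally be worse conditioned than independent columns.

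At n = p = 216 a square system can also be solved exactly for any outcome. In one run with purely random labels, training accuracy was 100% and accuracy on 5,000 new samples was 49%.

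These results describe an unregularised linear system, which is what the protocol's argument invokes. A support vector machine is regularised and can be fitted with fewer samples than variables. So the rule fails on its own terms and is not a requirement of the named method.

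**3. The test allowance**

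An extra 10% of 216 is 21.6, about 22 infants. With n1 cases, n2 non-cases and A = 0.70, the Hanley-McNeil variance of the AUC is

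SE² = [A(1−A) + (n1−1)(K1−A²) + (n2−1)(K2−A²)] / (n1·n2),

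with K1 = A/(2−A) = 0.5385, K2 = 2A²/(1+A) = 0.5765 and A² = 0.49.

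At 50%, n1 = n2 = 11: SE² = (0.21 + 10 × 0.0485 + 10 × 0.0865)/121 = 0.0129, SE = 0.114, half-width = 1.96 × 0.114 = 0.22.

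| Assumed MARI rate | Cases among 22 | 95% half-width | Lower limit |
|---|---|---|---|
| 10% | 2.2 | 0.41 | 0.29 |
| 20% | 4.4 | 0.30 | 0.40 |
| 30% | 6.6 | 0.26 | 0.44 |
| 50% | 11 | 0.22 | 0.48 |

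The lower limit is below 0.5 in every row. Taking the test set as 10% of 247, about 25 infants, gives a half-width of 0.21 and a lower limit of 0.49 at the 50% rate.

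**4. Using all 250 dyads**

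- 10% rate (25 cases, 225 non-cases): SE² = (0.21 + 24 × 0.0485 + 224 × 0.0865)/5625 = 0.00369, SE = 0.061, half-width 0.12.
- 50% rate (125 and 125): SE² = (0.21 + 124 × 0.0485 + 124 × 0.0865)/15625 = 0.00108, SE = 0.033, half-width 0.06.

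These are approximate, because cross-validated predictions are not fully independent.

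**The case against.** The strongest reply is that little of practical consequence is wrong. The arithmetic gap is 2 to 3 samples and the planned 250 absorbs it; that stands, and it makes the total a side note. Study C serves secondary objectives 6 to 11, some of them descriptive or hypothesis-generating, and the primary analysis in section 7.1 is untouched; that also stands and limits the severity.

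Three stronger readings are tempting but not supported.

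- **That 247, or even 250, breaks the protocol's own rule and 253 are needed.** This comes from 216/(0.90 × 0.95) = 252.6, which treats the 10% as a share of the total and the 5% as lost infants. The text speaks of extra samples and of measurement error. Adding 22 test infants and losing none, 247 leaves 247 − 22 = 225 for training, above 216.
- **That the test set will hold about two cases.** This borrows the 10% rate from Study A's sample size, which is for medically attended lower respiratory tract infection. Study C's endpoint is the broader MARI, with no stated rate, so two cases is only one end of an assumed range.
- **That the protocol commits to one fixed split.** It says only that the analysis is divided into training and testing. Repeated splits are not excluded, and an analysis plan that is not shown may specify them.

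The reply does not rescue the rationale. The 1:1 claim is a wrong statement in the protocol, not a detail left open. The test allowance is likewise a figure the protocol gives, and it is too small at every rate examined.

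**Conclusion.** The concern holds in this form. The reason given for Study C's size is unsound: a 1:1 ratio is the worst-conditioned point for an unregularised system (median condition number about 800 at n = 216, against 5.6 at n = 432), and the named method does not require it. What remains is a number with no stated link to performance or precision. The test allowance of about 22 infants could not separate an AUC of 0.70 from chance at any MARI rate from 10% to 50%.

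The conditioning figures rest on independent normal columns. The precision figures rest on the assumed AUC, the assumed rates and the Hanley-McNeil approximation. The mismatch between 246.1 and 249 or 250 is a minor slip. None of this shows that 250 dyads are too few. The point is worth correcting but is not a must-fix.

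**What to change.** Keep 250 dyads and rewrite the Study C paragraph of section 4.4:

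- Delete the claim that a 1:1 ratio avoids ill-conditioning.
- Reconcile the variable count (214 or 216) and correct the total.
- State that performance of the regularised model will be assessed by repeated nested cross-validation over all dyads, instead of relying on a hold-out of about 22.
- Name the outcome to be classified, and justify 250 by the expected precision over a stated range of MARI rates, for example an AUC half-width of about 0.12 at 10% and 0.06 at 50%, labelled as approximate.

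The cost is one reworded paragraph and a little more computing time. No extra participants, samples or questionnaires are needed.

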**Study C**

A 24h recall is filled in on the day of collection of the 1 and 3 month breast milk sample, to determine the short-term effect of maternal diet on breast milk composition. The FFQ is filled in at 2 and 4 months, to determine the long-term effect (dietary pattern) on breast milk composition. The 4 month FFQ is a repetitive measurement to evaluate whether the maternal diet has changed since 2 months, and therefore also can be linked to the 3 month breast milk sample. A change in dietary pattern is conceivable because, for example, the mother has stopped breastfeeding and/or maternity leave from work has ended.

Feces and saliva are collected at 3 months because at this time point the effect of the breast milk composition is expected to more significant that at 1 month or 1 week postpartum. The 3 month time point is also more suitable than the 6 month time point because by that time, infants may have received solid foods aside of breast milk and/or infant formula.

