## Replacement of individual subjects after withdrawal

A new mother-child dyad will be recruited to replace a withdrawn dyads when withdraw occurs before the first sample is taken.

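### Study C's 250 dyads leave a margin of three over its own minimum of 247, with no allowance for losses before the 3-month milk sample

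*Protocol*

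**What the plan says.** Section 4.4 of the Protocol derives the Study C size from the 24h recall, which "has the largest number of variables at 216 variables". It then applies a rule of thumb: "we need to have 1:1 relationship between variables and samples". Two additions follow. The first is that "we need an extra 10% of samples for testing"; the second is that "considering a measurement error of 5% puts the total of samples at 246.1", rounded up to 247. The conclusion reads: "Thus, we need at least 247 samples for the analysis of the dataset".

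The planned number stands in section 1, Study C: "In this cohort (n=250), we will additionally assess the maternal diet, and collect feces and saliva of the infant".

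Four other places bear on how many dyads will have usable 3-month data:

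- Section 4.2 asks only that parents intend to breastfeed to at least 3 months.
- Section 3, Study C, ties the 24h recall to the 1-month and 3-month milk samples. It justifies the repeat food frequency questionnaire at 4 months by a possible change of diet since month 2, for instance because "the mother has stopped breastfeeding and/or maternity leave from work has ended".
- Section 5.4 limits replacement: "A new mother-child dyad will be recruited to replace a withdrawn dyads when withdraw occurs before the first sample is taken". Under section 8.2 the first milk sample is taken at the initiation visit, within the first week after birth.
- Sections 7.2 and 7.4 provide for missing data in the recalls and for parents who stop returning questionnaires.

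**The concern.** A number described as the minimum for analysis should be the number that reaches the analysis. Here the planned cohort and the minimum are almost equal, and neither addition in the calculation is described as an allowance for loss. A mother who no longer breastfeeds at 3 months has no milk to pair with her 3-month recall. Under section 5.3.1, withdrawal is foreseen only where no properly stored milk sample exists at all. A dyad with a first-week sample and no 3-month sample therefore stays in the study, is not replaced, and contributes no 3-month pair.

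What is at stake is the credibility of the stated size for the 3-month diet-milk analysis. Section 1 presents Study C as meeting a need for a larger study whose size rests on a calculation.

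A second, smaller issue concerns the infant samples. Section 3 places stool and saliva at 3 months because the influence of milk composition is expected to be stronger then than earlier, and because solid foods may intervene by 6 months. An infant weaned before 3 months does not fit that reasoning. Including such infants without regard to feeding would be expected to weaken a milk-mediated association. That is a reasoned direction; the documents allow no estimate of its size.

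**Working it through.** **Inputs from the Protocol.** Variables: 216. Examples per variable: 1. Extra for testing: 10%. Measurement error: 5%. Stated minimum: 247 (all section 4.4). Planned dyads: 250 (section 1). Loss or weaning rate for Study C: none given.

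**1. The plan's own figure.** The text does not say how the two percentages are combined. The natural readings are:

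- 216 × 1.10 × 1.05 = 249.48, rounded up to 250
- 216 × 1.15 = 248.4, rounded up to 249
- 216 × 1.10 / 0.95 = 250.1, rounded up to 251
- 216 / 0.90 × 1.05 = 252
- 216 / 0.90 / 0.95 = 252.6, rounded up to 253

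None gives 246.1 exactly (246.1 / 216 = 1.139), but all lie within 3% of 247. I treat 247 as reproduced within tolerance and use it below. The first reading would leave a margin of zero, and the last three would exceed 250 before any loss.

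**2. Margin.** 250 − 247 = 3 dyads. 3 / 250 = 1.2%, so 247 / 250 = 98.8% must be retained. A fourth loss leaves 246.

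**3. Effect of loss on the 3-month pairs, counted per dyad.** The loss rates d are assumptions. Expected pairs are 250 × (1 − d). The chance of keeping at least 247 is the binomial probability of at most 3 losses among 250, with losses treated as independent. The enrolment that would preserve 247 is 247 / (1 − d), rounded up.

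| Assumed loss d | Expected pairs | Chance of at least 247 | Enrolment to preserve 247 |
|---|---|---|---|
| 1.2% | 247.0 | 65% | 250 |
| 2% | 245.0 | 26% | 253 |
| 5% | 237.5 | 0.1% | 260 |
| 10% | 225.0 | practically 0 | 275 |
| 20% | 200.0 | practically 0 | 309 |

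**4. The most generous reading of the 5%.** Suppose it were really a loss allowance. The need before loss would be 216 × 1.10 = 237.6, or 238, with 250 − 238 = 12 dyads spare. The chance of keeping 238 is then 52% at 5% loss and 0.2% at 10%. The margin is still inadequate at 10%.

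**5. If the recall-milk pair is the unit.** Pooling both time points gives up to 2 × 250 = 500 pairs. With 20% lost at 3 months only, 250 + 200 = 450 remain, well above 247. The two pairs from one mother are not independent examples, however, and section 4.4 does not mention pooling.

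**6. Which analyses lose numbers through weaning.** The 3-month recall-milk analysis does, because there is no milk. The 1-month recall-milk analysis is untouched by weaning after month 1. The diet-to-microbiota analysis is also untouched in number: stool is taken from the diaper, and the diet questionnaires are sent by e-mail. Loss to follow-up, unlike weaning, would reduce that count too.

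**The case against.** The strongest objection is that 247 is not a power threshold. It comes from a one-to-one rule of variables to samples, and section 4.4 itself concedes that the number needed depends on the data. No power or error rate changes when 247 becomes 246 or 238, so the probabilities above describe only the chance of meeting the plan's own figure. That stands. The point is that the plan states a minimum it has not provided for; no quantified statistical loss has been shown.

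Three stronger readings are tempting, and the documents do not support them:

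- **That the protocol expects mothers to wean before the 3-month sample.** Section 3 only calls a change of diet between months 2 and 4 conceivable and offers stopping breastfeeding as one example. A mother who stops at three and a half months fits that sentence and still gives the 3-month milk. Entry also requires an intention to reach 3 months. Weaning is foreseen as possible, and no rate is given.
- **That the stated size is certainly missed.** Section 4.4 never says whether a sample is a dyad or a recall-milk pair, or which time point it refers to. The closeness of 247 to 250 suggests the dyad, but that is an inference.
- **That every 3-month analysis falls short.** Weaned dyads still supply stool and diet data, so weaning does not shrink the diet-to-microbiota count.

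It may also be said that rules for analysing weaned dyads belong in a statistical analysis plan, which is not at hand. That is fair, and their absence is not raised as a defect. The relation between 247 and 250, by contrast, is fixed in the Protocol itself.

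**Conclusion.** The point holds in a limited form. Study C plans 250 dyads against its own minimum of 247, a margin of 1.2%, with no stated allowance for weaning, missing recalls or loss to follow-up and no replacement after the first-week sample. Taking the dyad as the unit, the 3-month recall-milk data set is expected to fall short at any loss above 1.2%, and at 5% it almost certainly would. This rests on assumed loss rates, on independent losses, and on an interpretation of the unit that section 4.4 leaves open. It does not extend to the 1-month pairs, and weaning does not bring the diet-to-microbiota count into it. Study C serves secondary objectives, so the primary objective of Study A is unaffected. The statement of size should still be corrected, because the correction is cheap and the present text promises a 3-month number that ordinary losses would undo.

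**What to change.** In section 4.4, Study C:

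1. Say whether the unit is the dyad or the recall-milk pair, and to which time point the 247 applies. If pairs are pooled over time points, say so and acknowledge that pairs from one mother are correlated.
2. State the size as 250 enrolled, with the expected analysable number at 1 month and at 3 months under a named loss assumption. For example, 10% to 20% loss by month 3 gives 225 to 200 pairs.
3. No longer present 247 as the delivered size of the 3-month diet-milk analysis.
4. While the text is open, show how 216, 10% and 5% lead to 246.1.

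For the 3-month diet-to-microbiota link, keep all infants in the main analysis. Use the feeding data from the two-weekly questionnaire (section 5.2) to adjust or stratify by current breastfeeding, with the still-breastfed subset as a sensitivity analysis. Making that subset the main analysis would select on feeding status after enrolment and could introduce bias. This may be recorded in the Protocol or in the statistical analysis plan.

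The cost is wording and a less favourable stated 3-month size. No added enrolment and no new data collection are needed. Enrolling enough to preserve 247 would be a different choice: 260 dyads at 5% loss or 275 at 10%.

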# METHODS

## Study parameters/endpoints

### Main study parameter/endpoint

- Parent-reported medically attended respiratory tract infection during the first year of life.

### Secondary study parameters/endpoints (if applicable)

**Study A:**

- Other infections during the first year of life (non-MARI respiratory tract infections but also gastro-intestinal infections).
- Allergies developed during first year of life.
- Gut discomfort of the infant during the first 6 months of life.
- Breast milk composition: antibody repertoire, oligosaccharides, immune cell repertoire (n=1000), extracellular vesicles (n=15).

**Study B:**

- Antibody repertoire in amniotic fluid, cord blood, maternal blood and infant’s saliva.
- Oligosaccharide, extracellular vesicles, antibody and immune cell repertoire in blood and amniotic fluid.

**Study C:**

- Diet(ary pattern) of the lactating mother.
- Fatty acid, protein, amino acid, fat- and water soluble vitamins and fibres composition in breast milk.
- Microbial composition of infant’s feces.
- Antibody repertoire and viral genome of infant’s saliva.

### Other study parameters (if applicable)

Other parameters that will be measured are:

- Complications and medication use during pregnancy and during labour.
- Birth characteristics (e.g. birth weight, Apgar score)
- Feeding habits (e.g. high allergenic food during pregnancy and first feeding of child)
- Household characteristics (e.g. age and amount of other children in household, pets etc.)
- Smoking habits of parents
- General information of parents (age, genetic background, education level, presence of (chronic) diseases and allergic status)
- Vaccination status mother

See for all questions the baseline and 2-weelky questionnaire.

## Study procedures

*Breast milk sampling:*

Women who participate in this study are asked to express and collect a whole milk sample from both breasts. The sample will be mixed by gently tilting the flask. After mixing, 5-10mL of the whole sample will be stored in a 50mL Falcon tube in the fridge. Parents are asked to note the date, time of expression and storage temperature on the tube. Samples will be handed in to the researcher during a house visit. The researcher will note the moment (1 week, 1, 3 or 6 month postpartum) and type (fore-, hind- or whole milk) of breast milk sample. The researcher will transport the sample to the UMC Utrecht. (Miller2013) The optimal processing conditions to fractionate the samples were tested in a pilot, see our SOP for more details about the processing of human milk samples before storage.

**Study C:**

For the breast milk sampling from mothers participating in study C, mothers are asked to collect a breast milk sample on the morning of collection before breakfast. This is asked because the assessment for the short-term influence of the maternal diet (24h recall) concerns the day before collection.

*Cord blood sampling:*

Cord blood is sampled from the umbilical vein, following the delivery of the child. First the umbilical has to be double clamped 3-5cm from the umbilicus to transect the umbilical cord. The child will consequently be removed from the field. The cord will now be prepared for blood sampling using a povidone iodine applicator to sterilize the umbilicus. Next, the needle will be inserted in the umbilical vein, standard blood sampling tubes will be used to collect the cord blood. The blood can be collected both *in utero* or *ex utero*. Meaning the venipuncture can be performed after or before the placental delivery. (Amson2015)

*Amniotic fluid collection:*

After rupturing the amniotic sac, amniotic fluid will be collected (regular procedure at the obstetric ward). The amniotic fluid will be stored at room temperature until retrieved by the researchers. For the study, about 200mL cord blood will be collected. 100ml will be used for cell analysis. About 9 vials with 1x10^7 cells each will be stored in the biobank, the other 1x10^7 cells will directly be used for FACS analysis. The remaining 100ml will be used to obtain serum. We will use about 1-2mL of serum to measure antibodies and HMOS, the remaining serum will be stored at the biobank facility of the UMC Utrecht.

*Venipuncture:*

Maternal blood samples will preferable be collected during the first house visit and not at delivery. We will collect venous blood samples from the median cubital vein.

We will analyse these blood samples on various components. The antibody composition will be performed in the group of [name] (LTI, UMC Utrecht) using ELISA or multiplex approaches. Oligosaccharide composition wil be measured in the group of [name] (LTI UMC Utrecht and Nutricia). Immune cell repertoire will be analysed in the group of [name] and/or [name] (LTI, UMC Utrecht) using flow cytometry. Extracellular vesicles will be measured at the group of [name] (Faculty of veterinary medicine, Utrecht University). We will collect about 70mL blood. We will collect five 10mL sodium-heparin tubes, of which one will be used for FACs analysis. The other tubes will be stored at the biobank. We will also collect two 10mL serum tubes. 1-2mL of the serum will be used for antibody and HMOS analysis, the remaining serum will be stored at the biobank facility of the UMC Utrecht.

*Saliva sampling:*

